### Statistical methods

The TASTE study is an explorative, hypothesis-generating study. Hence, there will be no formal hypothesis testing. Statistical analysis will be performed using a recognized statistical package such as SPSS. A significance level of α = 0.05 (two-sided) will be used and statistical adjustments for multiple testing will be considered. Descriptive statistics will be applied for description of the study cohort, the results of the (semi-) objective and subjective study assessments, and the dose to the taste bud bearing tongue mucosa and the salivary glands. Univariable, binary logistic regression analysis will be performed to test for a significant correlation of clinical and dosimetric variables, smell assessment, saliva output and composition with the primary endpoint (subjective taste impairment at 12 months post therapy). Multivariable NTCP model development will be performed with stepwise forward selection, based on likelihood-ratio, to select the most important predictor(s).

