## Abstract

**Background:**

One of the main side effects of radiation therapy to the head and neck region is altered taste sensation. This causes significant morbidity and has profound effects on the quality of life (QoL) of patients. While radiation-associated toxicities like xerostomia and dysphagia are part of large investigations, data on taste impairment is sparse. Small cohort sizes in the majority of studies and a variety of analysis methods limit our current understanding of the underlying processes. None of the studies published to date used a taste-specific QoL questionnaire with differentiation of the different taste qualities (e.g. sour, bitter). Furthermore, data regarding the correlation of taste impairment with radiation-associated change in saliva composition is currently not available. The aim of the TASTE study is to fill this gap. Based on the acquired data, a normal tissue complication probability (NTCP) model for late radiation-associated taste impairment will be developed.

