**Methods:**

In this prospective, observational multicenter study 150 head and neck cancer patients undergoing radiation therapy will be recruited and undergo repetitive (semi-) objective and subjective assessment of their taste, smell and salivary function (questionnaires, taste and smell assessment, saliva analysis). Primary endpoint will be patient-reported taste impairment 12 months post radiation therapy using a standardized questionnaire. Secondary endpoints will include taste impairment measured using taste strips at 12 months and 2 years post radiation therapy. Differences between subgroups (radiation side, chemotherapy, etc.) and changes over time will be assessed while adjusting for confounding factors (e.g. age, sex, smoking history).

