### Objectives

Addressing the current lack of reliable data, the TASTE study aims to provide more detailed information on taste impairment in patients undergoing radiation therapy to the head and neck region. The objectives are as follows:

Primary objective: To develop a normal tissue complication probability (NTCP) model for late radiation-associated taste impairment, taking into account dose-volume histogram (DVH) data of the taste bud bearing tongue mucosa and salivary glands, baseline taste status, and baseline salivary gland function.Secondary objectives:

To longitudinally investigate changes in taste and smell associated with radiation therapy using standardized taste strips, sniffing sticks and QoL questionnaires.To evaluate the effects of the radiation dose to the taste bud bearing tongue mucosa on different taste qualities.To investigate the correlation between radiation dose to the salivary glands and saliva production/composition, and its impact on taste impairment.To analyze if radiation-associated taste impairment mid- or end of treatment predicts for late taste impairment.To define dose constraints for the taste bud bearing tongue mucosa and salivary glands with the goal of designing a study to evaluate a taste-preserving radiotherapy in head and neck cancer patients.

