Taste impairment has been shown to be significantly correlated to patient-reported xerostomia using QoL questionnaires [11]. A significant correlation between the mean dose to the parotid glands and taste impairment has been postulated [12, 13, 17], but to date the data remains conflicting. Chen et al. showed that the mean radiation dose to one or both parotid glands predicts taste impairment [12]. In contrast, Fernando et al. found no correlation between the volume of the irradiated parotid glands (bilateral) and taste impairment and concluded that irradiation of the tongue is the primary causative factor of dysgeusia rather than radiation-induced xerostomia [9]. Furthermore, different patterns have been shown between taste impairment and salivary dysfunction, with the latter often being more long-lasting [31]. It should be noted that studies analyzing the correlation between taste impairment and xerostomia thus far used a variety of different assessment methods which limits comparability. Overall, taste-specific studies correlating taste with sialometry are rare, often with small patient cohorts [14], and most do not consider the dose received by the salivary glands as a variable. The TASTE study aims to fill this gap.

Information on how radiation-associated changes in saliva composition and pH changes affect taste is also lacking to date. Decreased salivary pH [21, 32, 33], as well as dynamic changes in electrolyte composition [33] and salivary proteins such as amylase [34] during and after radiotherapy have previously been demonstrated [35]. As salivary constituents interact with tastants and taste receptors, they play an important role in taste sensitivity. Salty taste is dependent on the background levels of sodium chloride that taste receptors are adapted to. Changes in pH, and thus free hydrogen ions, will alter sour taste. Amylase levels might affect perceived sweetness. Bitter taste has been associated with proline-rich proteins [36].

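### The univariable tests of saliva and salivary-gland dose against 12-month taste are open to confounding by tongue dose, and forward selection does not guarantee a tongue-adjusted estimate for the saliva objective

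*Protocol article*

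**What the plan says.** The Statistical methods section names two steps for the primary endpoint, patient-reported taste impairment at 12 months. The first is one variable at a time: "Univariable, binary logistic regression analysis will be performed to test for a significant correlation of clinical and dosimetric variables, smell assessment, saliva output", continuing to saliva composition. The second is: "Multivariable NTCP model development will be performed with stepwise forward selection, based on likelihood-ratio, to select the most important predictor(s". Neither sentence says that a variable is kept in regardless of its p-value. On error control the section says: "A significance level of α = 0.05 (two-sided) will be used and statistical adjustments for multiple testing will be considered".

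The Objectives section gives the NTCP model a joint content, "taking into account dose-volume histogram (DVH) data of the taste bud bearing tongue mucosa and salivary glands, baseline taste status, and baseline salivary gland function". It also lists a separate secondary objective: "To investigate the correlation between radiation dose to the salivary glands and saliva production/composition, and its impact on taste impairment". Another secondary objective is to define dose constraints for the tongue mucosa and the salivary glands.

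The Discussion presents conflicting earlier evidence. Some studies link parotid dose to taste loss. One cited study concluded that "irradiation of the tongue is the primary causative factor of dysgeusia rather than radiation-induced xerostomia". The article offers this study as a way to fill that gap.

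**The concern.** Separating a tongue effect from a gland or saliva effect needs an estimate of one with the other held fixed. The univariable tests cannot give that. Tongue-mucosa and gland doses come from the same treatment plan. If they rise together, gland dose partly stands in for tongue dose, and so does saliva, which falls with gland dose. A significant univariable saliva or gland result would then be expected even if neither had any influence on taste.

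The forward-selected model is the only stated route to adjustment, and selection answers a different question. It picks predictors. Among correlated candidates it may keep the wrong one. A candidate that is left out gets no adjusted estimate or confidence interval, so a reader cannot tell an absent effect from an undetected one.

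At stake are the interpretation of the saliva objective and the basis of any gland dose constraint for taste that is carried into a later study.

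**Working it through.** The article gives no dose correlation, event rate or effect size, and its sample of 150 has no formal calculation. There is therefore no figure of its own to reproduce, and the size of the problem has to be shown over a range.

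**Inputs from the article**
- Up to 150 patients (Sample size).
- Two-sided 0.05 level, univariable logistic tests, forward likelihood-ratio selection (Statistical methods).
- Tongue-mucosa and gland doses are both recorded (Collection of clinical data).

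**Assumed inputs**
- 150 or 120 patients analysed.
- 30% impaired at average tongue dose.
- Tongue odds ratio (OR) of 1.5, 2.0 or 2.5 per SD of dose.
- Tongue–gland dose correlation ρ of 0.3, 0.5, 0.7 or 0.8.
- Gland dose–saliva correlation of −0.6.
- No true effect of gland dose or saliva on taste.

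**Model**, in standardised variables with independent standard normal e₁ and e₂:
- Tongue dose T is standard normal.
- Gland dose G = ρT + √(1 − ρ²)·e₁.
- Saliva S = −0.6·G + 0.8·e₂.
- logit P(impaired) = log(0.3/0.7) + log(OR)·T.

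The saliva–tongue correlation is −0.6 × ρ, that is −0.18, −0.30, −0.42 and −0.48 at the four values of ρ. Saliva is thus a weaker stand-in for tongue dose than gland dose is, and it should be misattributed less often.

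**Check.** There were 1,000 runs per scenario. The Monte Carlo standard error near 5% is √(0.05 × 0.95/1000) = 0.7 percentage points. Forward selection chose among T, G and S.

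Results for 150 patients and tongue OR 2.0, as % of runs:

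| ρ | Gland, univariable | Saliva, univariable | Gland, T forced in | Saliva, T forced in | Forward: T kept | Forward: gland or saliva without T |
|---|---|---|---|---|---|---|
| 0.3 | 19 | 11 | 5 | 6 | 95 | 1 |
| 0.5 | 43 | 19 | 4 | 5 | 94 | 3 |
| 0.7 | 72 | 31 | 5 | 6 | 90 | 7 |
| 0.8 | 84 | 41 | 6 | 6 | 83 | 15 |

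Ranges over all 24 scenarios:
- Univariable gland test significant: 9–97%.
- Univariable saliva test significant: 6–58%.
- Forward selection of gland or saliva without tongue dose: 0–19%. The 19% arises with a weak tongue effect (OR 1.5) and ρ = 0.8.
- With tongue dose forced in: gland 3–7%, saliva 4–7%.

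**When saliva does matter.** In a further check with 120 patients, tongue OR 2.0, ρ of 0.4 to 0.8 and a true OR of 1.5 per SD lower saliva, forward selection left saliva out in 58–63% of runs. A forced model would also often miss significance at this sample size. What it adds is an estimate and interval in every case.

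**The case against.** The strongest reply is that tongue dose is not missing from the plan. The sentence after the univariable one introduces a multivariable model, and the primary objective places tongue and gland dose–volume data in it together. A reader who stops at the univariable sentence might infer that saliva and gland dose are only ever tested without tongue dose, so that misattribution is certain and the tongue-versus-saliva question stays unanswered. The article does not support that. Under the assumed inputs, forward selection usually removes the false signal. This part of the objection stands and limits the point.

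Four further parts also have weight:
- The abstract's Methods paragraph says "changes over time will be assessed while adjusting for confounding factors (e.g. age, sex, smoking history". It would be tempting to read this as excluding tongue dose. The list is open, and it concerns subgroup differences and change over time, not the saliva tests.
- The abstract's Background names a gap on "correlation of taste impairment with radiation-associated change in saliva composition", and a reader might infer that the plan analyses 12-month level instead of change. The article does not say which visit or which form of the saliva measure enters the regression, and it lists baseline gland function for the NTCP model.
- The dose correlation is assumed. Eligibility rests on tongue mucosa or at least one major gland receiving 5 Gy or more, and unilateral treatment is included. Either could weaken the correlation.
- The study is exploratory, and nothing says a constraint would come from a univariable result.

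It can also be said that covariate sets belong in a fuller document that is not shown. That holds for detail. It does not cover a method the article itself states, when that method is poorly suited to an objective the article itself states. The exploratory label lowers the severity but does not remove confounding.

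**Conclusion.** The point holds in limited form. The univariable saliva and gland-dose tests are open to confounding by tongue-mucosa dose. The forward-selected model reduces this without guaranteeing that tongue dose is retained, and it does not promise an adjusted saliva estimate. The saliva objective and the question raised in the Discussion are therefore partly served, not lost.

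The univariable tests can be close to nominal (6% for saliva, 9% for gland dose) when the tongue effect and the dose correlation are weak, and far above it (58% and 97%) when both are strong. After forward selection the error falls to at most 19%. All these figures rest on assumed correlations, effect sizes and event rate, and on only three candidate predictors where the study will have more. The direction follows from the design once the doses are correlated; the size cannot be fixed from the article.

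**What to change.** In Statistical methods, add for the saliva objective two prespecified logistic models of 12-month taste impairment, each with tongue-mucosa dose and baseline taste always included:

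1. **Gland-dose model:** gland dose, without post-treatment saliva, because saliva may lie on the path from gland dose to taste.
2. **Saliva model:** the chosen saliva measure, with baseline saliva also included.

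Report both adjusted estimates with confidence intervals whether or not they are significant. Label the univariable saliva and gland-dose results as unadjusted. Do not base a gland dose constraint for taste on a model that omits tongue dose. Do not read the change in the gland-dose odds ratio with and without saliva as the share that runs through saliva: odds ratios are non-collapsible, so the coefficient can move without any mediation.

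The cost is wording. Tongue and gland doses, baseline taste and baseline saliva are already collected. The downside is wider confidence intervals where the doses are collinear, and these show how little the data can separate the two.

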### Sample size

The TASTE study is primarily designed as an explorative, hypothesis-generating study. As there is no formal hypothesis testing, no formal sample size calculation has been performed. We aim to recruit 150 head and neck cancer patients referred for radiation therapy with curative intent. To our knowledge, this constitutes a larger sample size than any other study published so far that investigated the dosimetric impact on taste using the taste bud bearing tongue mucosa and major salivary glands as OAR structures [17] or used semi-objective taste testing in addition to PROMs [11, 14]. Furthermore, this will represent the largest cohort to date with analysis of radiation-associated saliva changes. Thus far, studies investigating changes in saliva composition after radiotherapy to the head and neck region included a maximum of 138 patients [21].

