### Outcomes

The primary endpoint is defined as the patient-reported taste impairment assessed by the MDASI-HN (MD Anderson Symptom Inventory Head and Neck module) questionnaire 12 months post-treatment. By choosing this time point we will be able to assess late radiation-associated taste impairment.

Secondary endpoints are taste impairment diagnosed using taste strips at 12 months and 2 years post-treatment, as well as patient-reported taste impairment 2 years post-treatment.

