In addition to taste impairment in general, we will evaluate the effects of the radiation dose to the taste bud bearing tongue mucosa on different taste qualities. The specific qualities of taste are known to result from activation of different types of taste cells via distinct receptors and signaling pathways [6]. Therefore, radiation might affect taste qualities differently depending on the underlying pathomechanism. Besides validated taste assessment with taste strips, the participants are asked to complete a taste-specific questionnaire focusing on changes in the different taste qualities. Few studies have analyzed the effect of radiotherapy on individual taste qualities, with often conflicting results. Some studies reported that bitter and salty taste qualities were affected the earliest and more severely in head and neck cancer patients undergoing radiotherapy [31, 38]. Only sour taste was significantly impaired after radiotherapy in another study, while bitter, salty, and sweet tastes were not [15]. Sweet taste appeared to be the most robust in those studies. However, Asif et al. found that sweet and salty taste decline significantly, whereas they only found a trend with bitter, and no change with sour [14]. Yamashita et al. reported an equal impairment pattern of all four basic tastes, as well as umami [39], while the impairment pattern of umami significantly differed from that of the other four taste qualities in another study [41].

Ultimately, the objective of the TASTE study is to develop a NTCP model for late radiation-associated taste impairment. We intend to define dose constraints for the taste bud bearing tongue mucosa and salivary glands. The results of the study may then be further used to evaluate taste-preserving radiotherapy for patients with head and neck cancer, which could significantly reduce the long-term burden in this patient cohort.

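### Building the NTCP model by forward stepwise selection is likely to give over-optimistic performance, poor calibration and an unstable choice of dose metric

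*Protocol article*

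**What the plan says.** All references are to the protocol article.

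- **Objectives.** The primary objective is an NTCP model that uses DVH data of the tongue mucosa and salivary glands, baseline taste and baseline salivary function.
- **Statistical methods, first step.** "Univariable, binary logistic regression analysis will be performed to test for a significant correlation of clinical and dosimetric variables", together with smell results and the amount and make-up of saliva.
- **Statistical methods, second step.** "Multivariable NTCP model development will be performed with stepwise forward selection, based on likelihood-ratio, to select the most important predictor(s". On error control: "A significance level of α = 0.05 (two-sided) will be used and statistical adjustments for multiple testing will be considered".
- **Outcomes.** "The primary endpoint is defined as the patient-reported taste impairment assessed by the MDASI-HN", taken at 12 months. The Questionnaires section gives the items a 0–10 scale; the logistic analysis treats the endpoint as binary.
- **Sample size.** "We aim to recruit 150 head and neck cancer patients referred for radiation therapy with curative intent". The reasoning is: "As there is no formal hypothesis testing, no formal sample size calculation has been performed". The number is supported only by comparison with the size of earlier cohorts.
- **Use of the model.** The Discussion says: "We intend to define dose constraints for the taste bud bearing tongue mucosa and salivary glands". The Objectives section ties these constraints to the design of a later study of taste-preserving radiotherapy.

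**The concern.** The absence of hypothesis testing is given as the reason for having no sample size calculation. That does not cover a prediction model, whose reliability depends on the number of events relative to the number of candidate parameters. Forward selection reuses the same few events to choose variables and to estimate their coefficients. It tends to admit variables with no effect, to exaggerate the coefficients of those it keeps, and to choose more or less by chance among correlated dose metrics.

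The last of these matters most here, because the study's practical product is a set of dose constraints. If another sample of patients would have selected a different organ or DVH metric, or if the slope of risk on dose is exaggerated, the error passes into the design of the next study.

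**Working it through.** The plan has no figure of its own to reproduce: 150 comes without an event rate, attrition rate or performance target.

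**1. Candidates named.** Counting one parameter per item:
- The Collection of clinical data section gives 14 besides dose: age, sex, site, tumour stage, nodal stage, laterality, chemotherapy, targeted therapy, tumour control, oral surgery, smoking, alcohol, comorbidities and medication.
- Dose to the tongue mucosa and three types of major gland adds 4.
- Baseline taste and smell add 2.
- Saliva volume and pH, each unstimulated and stimulated, add 4; electrolytes, proteins and amylase add at least 3.

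The sum is 14 + 4 + 2 + 4 + 3 = 27, or 26 without tumour control, which is known only after treatment. The narrowest reading, using only the inputs named in the primary objective, is 4 doses + 1 taste + 2 saliva volumes = 7 with a single dose metric per organ. With five metrics per organ (an assumption) it is 4 × 5 + 3 = 23.

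**2. Events.** Events = 150 × evaluable fraction × event rate. Neither rate is in the document; 70–100% and 20–50% are assumed.

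| Evaluable | Impaired | Events | Events per candidate: 20 / 30 / 40 |
|---|---|---|---|
| 105 (70%) | 20% | 21 | 1.1 / 0.7 / 0.5 |
| 120 (80%) | 35% | 42 | 2.1 / 1.4 / 1.1 |
| 150 (100%) | 50% | 75 | 3.8 / 2.5 / 1.9 |

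**3. Univariable screening.** If nothing mattered and tests were independent, the chance of at least one p < 0.05 is 1 − 0.95^k: 64% for k = 20, 79% for 30 and 87% for 40.

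**4. Parameters that the data can carry unpenalised.** For expected shrinkage S = 0.9, p = n(S − 1) ln(1 − R²/S). Here R² is the assumed Nagelkerke value times its maximum, 1 − exp{2[φ ln φ + (1 − φ) ln(1 − φ)]}, and φ is the event rate.
- φ = 0.20, Nagelkerke 0.15: R² = 0.15 × 0.632 = 0.095. With n = 120, p = 120 × 0.1 × 0.112 = 1.3.
- φ = 0.40, Nagelkerke 0.30: R² = 0.30 × 0.740 = 0.222. With n = 150, p = 150 × 0.1 × 0.283 = 4.2.

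So 120–150 evaluable patients support about 1 to 4 parameters. Twenty would need about 707 patients (second setting) to 1,796 (first setting).

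**5. Simulation of the stated method.** Forward likelihood-ratio selection with entry at p < 0.05 (assumed; the article gives no entry threshold), 120 patients, 20, 30 or 40 candidates including ten dose variables correlated 0.7, 150 runs per setting, tested on 4,000 new patients.
- Three true predictors: apparent AUC 0.76–0.80; in new patients 0.64–0.67; median calibration slope 0.39–0.55. The true dose variable was preferred to its correlated neighbours in only 35–50% of models.
- No true predictor, 30–48 events: at least one variable was selected in 49–84% of runs. When one was, apparent AUC was 0.65–0.70 against 0.50 in new patients.

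A further set with 20–26 candidates and 105–150 evaluable patients gave apparent AUC 0.73–0.76 against 0.63–0.65, with slope 0.43–0.62. Eight candidates still gave slope 0.66–0.79.

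**6. List length and fitting method separated.** Both methods were given the same list (120 patients, 35% events, four dose variables correlated 0.5, two true predictors with OR 1.73, 150 runs).

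| Candidates | New-patient AUC, forward / ridge | Median slope, forward / ridge |
|---|---|---|
| 6 | 0.67 / 0.67 | 0.77 / 1.08 |
| 26 | 0.63 / 0.62 | 0.44 / 1.10 |

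With OR 2.5 and six candidates, forward selection gave apparent AUC 0.80, new-patient AUC 0.78 and slope 0.93. A long list costs discrimination whichever method is used. Forward selection mainly costs calibration.

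**The case against.** **Silence in a condensed article.** A reader might infer that the trial plans no shrinkage, validation or limit on candidates. The document does not support that. The full protocol and analysis plan are not shown and may contain all three; one can say only that none is stated here. What stands is the method the article does commit to. Internal validation added elsewhere would measure the optimism, but would not by itself stabilise the choice among correlated doses.

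**The candidate pool.** The long variable list is attached to the univariable step. The article does not say that all of it enters the multivariable model, or that univariable significance is the filter. No DVH cut-points are named. Larger figures are therefore not supported: with 76 candidates and two modest effects, simulation gives apparent AUC 0.80 against 0.61 and slope 0.33, but 76 is not a number from the document. A fixed 30–55 events is likewise an assumption. The point survives the narrow reading in weaker form, since eight candidates still left the slope below 0.8 in the settings run.

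**Comparisons that flatter ridge.** Setting forward selection on a long list against ridge on a short list containing the true predictors mixes two effects. The same-list comparison is the fair one, and it shows no AUC advantage for ridge.

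**Exploratory purpose.** The study calls itself hypothesis-generating, does not influence treatment, and intends its constraints for designing a further study. This lowers the severity. It does not make an uncorrected model a sound source of constraints, because that model is the primary objective.

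**Conclusion.** The concern holds as a should-fix. The article commits its primary objective to likelihood-ratio forward selection, with about 20 or more possible candidates and a sample size that has no modelling basis. With about 20–40 candidates, apparent AUC is likely to exceed AUC in new patients by roughly 0.1 (about 0.73–0.80 against 0.63–0.67). The calibration slope is likely to be about 0.4–0.6, and the choice among correlated dose metrics unstable.

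These sizes rest on assumed event rates, attrition, effect sizes, correlations and entry threshold. The direction does not depend on the exact event count: even 75 events leave under four per candidate with 20 candidates. The loss shrinks with a short list and becomes small with strong effects as well. It would go too far to say that the model will certainly be overfitted or that the study cannot meet its aim.

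**What to change.** Replace the forward-selection sentence with the following.

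1. Before any outcome analysis, limit the candidate list to variables available at treatment planning. Tumour control after therapy drops out.
2. Keep the DVH data of the tongue mucosa and salivary glands, which belong to the primary objective. Group or reduce the correlated metrics without using the outcome. Cutting to one summary dose per organ would discard part of that objective, and the Discussion itself faults earlier studies for lacking systematic DVH analysis.
3. Fit penalised logistic regression (ridge or elastic net). Both parts are needed: the shorter list protects discrimination and the penalty protects calibration.
4. Bootstrap the whole procedure, including any selection, and report optimism-corrected AUC and calibration slope.
5. Derive dose constraints only from the shrunken model, with intervals and labelled provisional.

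If the full protocol or analysis plan already contains some of this, the remaining change is to bring the method sentence into line with it.

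The cost is some extra programming, possibly outside the SPSS menus, and a less favourable reported AUC. No extra patients or visits are needed. The Study status section projects recruitment to June 2026, so the change can be made before the 12-month outcomes are analysed.
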